### Sample size considerations

The sample size was estimated based on the primary endpoint of cumulative incidence of complications related to the baseline disease. The sample size analysis was computed with R software [24], following the approach described by Steen A. Julious for non-inferiority trials [25]. Although there is little available information regarding this outcome in the general population of chronic patients, we expect 10% of events in face-to-face consultations [26–28] and 12% in the remote consultation arm (based on routine practice of the research team). Assuming a type-I error of up to 2.5% and a statistical power of 80%, 1068 subjects per arm should be analyzed to reject the non-inferiority hypothesis with a non-inferiority margin of 2% and assuming 10% of participants lost to follow-up.

Altogether, the participating centers schedule 252,000 routine follow-up visits during a period equivalent to the study, corresponding to 121,400 different patients. Therefore, the recruitment of the estimated 2136 patients is considered within the capabilities of the participating centers.

Owing to the scarcity and heterogeneity of available data about the primary endpoint, a blinded interim analysis will be conducted when 50% of the total sample has been recruited to revise the assumptions used to calculate the sample size, as proposed in the E9 Guide of the ICH on Statistical Principles for Clinical Trials [29].

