**Methods:**

Multicenter, randomized controlled trial being conducted in four centers of an administrative healthcare area in Catalonia (North-East Spain). Participants will be screened from all individuals, irrespective of age and sex, who require follow-up in outpatient consultations of any of the departments involved in the study. Eligibility criteria have been established based on the local guidelines for screening patients for remote consultation. Participants will be randomly allocated into one of the two study arms: conventional face-to-face consultation (control) and remote consultation, either teleconsultation or video consultation (intervention). Routine follow-up visits will be scheduled at a frequency determined by the physician based on the diagnostic and therapy of the baseline disease (the one triggering enrollment). The primary outcome will be the number of adverse reactions and complications related to the baseline disease. Secondary outcomes will include non-scheduled visits and hospitalizations, as well as usability features of remote consultations. All data will either be recorded in an electronic clinical report form or retrieved from local electronic health records. Based on the complications and adverse reaction rates reported in the literature, we established a target sample size of 1068 participants per arm. Recruitment started in May 2022 and is expected to end in May 2024.

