### Data management and analysis

All data recorded in the eCRF will be stored in a REDCap platform hosted in a local server. The REDCap data will be transferred to a database, which will also contain the data extracted from the local EHR and the CHSS registries. All registries will be linked through the identification number of the Catalan Health Service.

Data recorded in the eCRF will be monitored for completeness and quality by a professional monitor working at the research office of the Hospital acting as sponsor. We will schedule periodic visits to assess the adherence of investigators to the study protocol and good clinical practices. The clinical monitor will release reports at the end of each visit.

A statistical analysis plan, with detailed analyses for each study outcome, will be performed after the last patient has attended the final visit and before the closure of the database.

The primary objective will be assessed using a non-inferiority analysis of the cumulative incidence of complications of the baseline disease between remote consultation (video and teleconsultation arms) and face-to-face consultation, using a non-inferiority margin of 2%. The analysis will be based on a modified binomial test to assess the non-inferiority of an experimental intervention vs. a control group in a three-arm trial [23]. The primary analysis will be conducted on a per-protocol study sample, which will include all participants who have finished the study and have not been withdrawn because of non-allowed visits using modalities other than scheduled. The intention-to-treat population, used for sensitivity analyses, will consist of all randomized patients completing at least one visit. Since the analysis will be based on an event rate, missing data will not be imputed.

The primary analysis will be replicated with patients stratified according to the following characteristics: hospital department, diagnostic, disease duration (chronic vs. acute or sub-acute), anatomic-therapeutic treatment groups, and GMA health risk group. The clinical and demographic characteristics of study participants will be described and compared between excluded/withdrawn participants.

The statisticians will be blinded for the allocation arm. The type I error will be set at 2.5% for the primary analysis and 5% for the rest of the analyses. All analyses will be conducted using R software (version 4.0 or higher) [24]. Data collected during the ECASeT trial will not be re-used.

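### The expected excess of complications (10% v 12%) equals the 2% non-inferiority margin, so 1068 per arm gives about 2.5% power, not 80%

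*Protocol article*

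**What the plan says.** All the inputs stand in the protocol article.

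- **Expected rates** (Sample size considerations): "we expect 10% of events in face-to-face consultations" and "12% in the remote consultation arm (based on routine practice of the research team").
- **Error rates** (same section): "Assuming a type-I error of up to 2.5% and a statistical power of 80"%. Data management and analysis agrees on the 2.5% for the primary analysis: "The type I error will be set at 2.5% for the primary analysis and 5% for the rest of the analyses".
- **Margin**: the primary analysis compares the cumulative incidence of complications between remote and face-to-face consultation, "using a non-inferiority margin of 2"%. Table 1 defines the outcome as the proportion of patients with an event.
- **Result**: "1068 subjects per arm should be analyzed to reject the non-inferiority hypothesis with a non-inferiority margin of 2"%, with 10% loss to follow-up, for a total of 2136. The Abstract repeats it: "we established a target sample size of 1068 participants per arm".

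A blinded review of the sample size assumptions is planned at 50% recruitment. The last paragraph of the Discussion presents the trial as adequately powered.

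**The concern.** A complication is a bad outcome. Remote care is non-inferior if its rate exceeds the face-to-face rate by less than 2 points. The plan expects an excess of exactly 2 points, so its working assumption lies on the boundary of the null hypothesis. There, a valid test declares non-inferiority with probability equal to its type I error, however many patients are enrolled.

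The trial's one confirmatory question is whether remote follow-up is safe. With this design it would be expected to fail under its own assumptions, and would probably fail even if the two modalities were equally safe. A failure to show non-inferiority could then be read as evidence of harm when it reflects only the size of the trial. If the interim review reuses the same formula, it repeats the problem.

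**Working it through.** **Inputs.** Face-to-face rate 0.10; remote rate 0.12; margin 0.02 (read as percentage points on the risk difference); one-sided type I error 0.025; power 0.80; loss 10%; 1:1 allocation (2136 = 2 × 1068).

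**1. Reproducing the plan's figure.** (1.960 + 0.8416)² = 7.849. Take a distance of 0.02 + 0.02 = 0.04 and the pooled rate of 0.11:

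n = 7.849 × 2 × 0.11 × 0.89 / 0.04² = 960.5, rounded up to 961

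961 / 0.9 = 1067.8, rounded up to 1068

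This matches exactly. With unpooled variance, n = 7.849 × (0.09 + 0.1056) / 0.04² = 959.5, giving 960 and then 1067. The match also shows that 1068 already includes the 10% loss, so 961 per arm are expected to be evaluable.

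Other readings, after 10% loss, do not give 1068:

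| Reading | Per arm |
|---|---|
| Equal rates of 10% / 11% / 12%, margin 2 points | 3925 / 4270 / 4606 |
| Superiority test, 10% v 12% | 4268 |
| Equal rates of 10% / 12%, margin 4 points | 981 / 1151 |

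**2. The correct distance.** For a harmful outcome the distance is margin − (remote − face-to-face) = 0.02 − (0.12 − 0.10) = 0. The formula divides by zero squared, so no finite n exists.

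**3. Power of the planned size.** Power = Φ((0.02 − δ)/SE − 1.96), where δ = remote − face-to-face and SE = √[(p_c q_c + p_r q_r)/n]. For equal 10% rates and n = 961, SE = √(0.18/961) = 0.01369; 0.02/0.01369 = 1.461; Φ(1.461 − 1.960) = 0.309.

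| Face-to-face | Remote | Power, 961 per arm | Power, 1068 per arm |
|---|---|---|---|
| 10% | 12% | 2.5% | 2.5% |
| 10% | 11% | 10.7% | 11.4% |
| 10% | 10% | 30.9% | 33.8% |
| 12% | 12% | 27.1% | 29.5% |
| 12% | 10% | 80.1% | 84.0% |

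Simulation at 961 per arm gives 2.6% at 10% v 12%, 31.1% at 10% v 10% and 80.2% at 12% v 10%. The stated 80% therefore belongs to the mirror image of the plan's assumption. With face-to-face held at 10%, 80% is reached at a remote rate of about 8.3%.

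**4. Size needed at equal rates.** At 10%: 7.849 × 0.18 / 0.02² = 3532 evaluable; 3532/0.9 gives 3925 per arm, 7850 in total. At 12%: 4145 evaluable, 4606 per arm.

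**5. What 961 per arm can deliver.** The 95% interval half-width is 1.96 × √(0.18/961) = 2.7 points at 10% in both arms and 1.96 × √(0.2112/961) = 2.9 points at 12%. Both exceed the margin, so the observed remote rate must be about 0.7 to 0.9 points below face-to-face for the upper limit to fall under 2 points. At equal rates, 961 per arm gives 80% power for a margin of √(7.849 × 0.18/961) = 3.8 points at 10%, or √(7.849 × 0.2112/961) = 4.2 points at 12%.

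**The case against.** - **The cause is inferred.** The R code and the cited sample size method are not shown, and the exact match needs a pooled variance that the article does not mention. This stands as a caution about how the figure arose. It does not affect the defect: 10% v 12% with a 2-point margin has no power, whatever code was run.
- **The 12% may only illustrate the margin, with equal rates intended.** This does not rescue the figure, because equal rates need about 3925 to 4606 per arm.
- **The 31% is conditional.** This is fair. It assumes a common rate of 10%, 961 analysed and a Wald-type test. Common rates of 10 to 12% and 961 to 1068 analysed give 27 to 34%. Much lower event rates would help: equal rates of 5% give 52% and 2.5% give 80% with 961 per arm. Those are far from the rates the plan assumes.
- **The planned modified binomial test was not modelled.** True, but no valid 2.5%-level test has more than about 2.5% power on the margin itself.
- **The interim review may catch it.** It is a real opportunity to correct the calculation. However, blinded data give a pooled event rate, not the difference between arms, so the review does not by itself reveal or remove the problem.
- **Speaking of rejecting the non-inferiority hypothesis is loose wording.** Agreed. The aim is clear elsewhere in the article, and this is a minor edit.

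**Conclusion.** The concern holds, and the stated power is wrong as written. Under the protocol's own rates and margin, power is about 2.5% instead of 80%, at any sample size. If the arms are truly equal at 10 to 12%, it is roughly 27 to 34%, so an equally safe remote service would miss non-inferiority about seven times in ten. The most likely origin is that the 2-point excess was added to the margin, the convention for a favourable outcome, when it should have been subtracted.

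The 2.5% rests only on the margin being 2 percentage points and the test having a valid one-sided 2.5% level. A relative reading of the 2% would be far stricter. The other power figures rest on a normal approximation with 961 to 1068 analysed per arm. The primary analysis is per-protocol and removes patients with non-allowed visits, so the number analysed may fall below 961 if such exclusions come on top of the 10% allowance.

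**What to change.** 1. Correct the calculation in Sample size considerations, taking the distance as the margin minus the expected excess. State that 1068 per arm (961 evaluable) gives 2.5% power at 10% v 12% and about 31% at equal 10% rates, with a 95% interval half-width of about 2.7 to 2.9 points.
2. Write the hypotheses with direction. H0: remote minus face-to-face is 2 points or more; H1: it is less than 2 points. Replace the wording about rejecting non-inferiority.
3. Reconcile expected rates, margin and size so that the expected difference lies inside the margin. Any change of margin needs its own clinical justification, made without sight of outcome data by arm, and should not be chosen to fit the sample. If neither size nor margin changes, say plainly that the trial will mainly estimate the difference with its interval.
4. Specify the correctly signed formula for the blinded re-estimation.
5. Remove the claim of adequate power from the Discussion.

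Steps 1, 2, 4 and 5 cost an ethics amendment and registry wording, and no patients. Trial status reports that recruitment continues and no interim analysis has been done, so there is time. Under step 3, keeping the 2-point margin with 80% power at equal 10% rates would mean about 7850 patients in place of 2136, some 3.7 times as many.

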### Interventions

Participants will be randomly allocated into one of the two study arms: control (i.e., face-to-face consultation) and remote consultation (including teleconsultation, and video consultation). All patients, irrespective of the consultation type, will receive short text message reminders a few days before the visit.

Participants allocated into the control arm will be scheduled with face-to-face appointments as usual. All phone calls (except reminders for scheduled visits) performed by the physician during the study will be noted in the electronic case report form (eCRF). Per protocol, participants allocated in the control arm can receive up to 25% of physician-doctor interactions by phone (that is, one phone call allowed for three face-to-face appointments).

Participants allocated in the remote consultation arm will be scheduled remote visits, either phone or video consultation. In case of phone visits, the physician will call the main phone number provided by the patient and, in case of not receiving an answer, other phone numbers listed as contact numbers. In case of video consultation, the participant will receive an additional text message with the visit link. When clicking the link, a website with the video consultation system embedded will open in the default browser of the user. The video consultation platform of the physician pops up a message indicating that the patient is in the virtual waiting room. Patients will remain in the virtual waiting room until the physician starts the visit. A technical assistance is readily available for physicians who experience troubles with the system. In case the patient does not show up to the video consultation after a reasonable time, the physician calls the patient by phone. The date and hour of the phone call and the reason for the inability to connect are recorded in the eCRF.

Participants allocated in the remote consultation arm that require face-to-face visits will be excluded from the per-protocol analysis, and the reason for the face-to-face visit will be recorded in the eCRF. Participants allocated in the remote consultation arm and scheduled with a phone visit cannot be visited by video, whereas those scheduled for a video consultation can undergo up to 25% of phone visits. Phone contacts and their reason in patients in the video consultation arm will be recorded in the eCRF.

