The definition of a candidate profile that is suited for remote consultation has been identified among the important challenges of remote consultation deployment [34]. In the research setting, this issue results in difficulty in defining the target population and, therefore, the selection criteria for recruitment. In response to the high demand for remote consultations in our area during the COVID-19 pandemic, the Catalan Health System developed a set of guidelines for helping clinicians and managers of healthcare centers implementing and offering video and teleconsultation appropriately [15, 35]. These guidelines, agreed by different stakeholders, recommend offering remote consultation only to patients without severe or unstable diseases. While these criteria exclude patients at higher risk of experiencing complications, they are unlikely to be offered remote consultation in the real world. Therefore, including them might result in a biased view of the safety of remote consultation in routine practice. Nevertheless, the applicability of the results obtained from our study shall be constrained to candidates to be followed up by remote consultation according to the local guidelines. Briefly, these guidelines identify as candidates all patients without severe diseases who are predisposed to contact the physician remotely.

Aside from the little precedent for making decisions on trial design, our study is challenged by the huge sample to be enrolled for achieving enough statistical power for a primary outcome that is expected to occur in a low frequency. Although the assumptions for sample size calculation will be revised in an interim analysis, as proposed by ICH E9 guidelines [29], recruiting such a huge number of patients is among the main risks of trial success. The risk of not reaching a sample size high enough for a powered analysis might be worsened by other aspects aside from recruitment, including a lower frequency of the primary outcome than expected, short follow-up periods established by the clinician, and high frequency of arm switch because of care needs.

In summary, the study protocol of this RCT, which is novel in assessing the safety of remote consultation as a primary endpoint in general consultations and with powered sample size, provides design insights that will hopefully aid researchers in making decisions in future trials for assessing remote consultation.

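### 1068 per arm is the number enrolled, not the number analysed, and the stated 80% power carries no stated allowance for the per-protocol exclusions beyond 10% loss to follow-up

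*Protocol article*

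**What the plan says.** The Sample size considerations section expects 10% of face-to-face patients and 12% of remote patients to have a complication, with a 2% margin. It continues: "Assuming a type-I error of up to 2.5% and a statistical power of 80%, 1068 subjects per arm should be analyzed", and ends the sentence with "should be analyzed to reject the non-inferiority hypothesis with a non-inferiority margin of 2% and assuming 10% of participants lost to follow-up". The next paragraph gives 2136 as the number to recruit, and the Abstract calls 1068 per arm the target sample size.

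The primary analysis set is per-protocol. Under Data management and analysis it consists of participants who finished the study and "have not been withdrawn because of non-allowed visits using modalities other than scheduled". The Interventions section adds: "Participants allocated in the remote consultation arm that require face-to-face visits will be excluded from the per-protocol analysis". It tolerates up to 25% phone contact in the control arm and up to 25% phone visits for video participants, and does not let phone-scheduled participants be seen by video. The Participant timeline section lists further reasons for discontinuation: in the remote arm, a clinical change calling for face-to-face care or failure to follow the remote procedures; in the control arm, a health status that makes travel inadvisable.

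The Discussion names "high frequency of arm switch because of care needs" among the things that might make an underpowered analysis more likely.

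**The concern.** Two statements about 1068 cannot both hold. If 1068 per arm are analysed after 10% loss, more than 2136 must be recruited. If 2136 are recruited, fewer than 1068 per arm are analysed.

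The allowance also does not match the analysis it is meant to protect. Loss to follow-up is one route out of the per-protocol set; visits in a non-allowed mode and mode-related discontinuation are others, and nothing is stated for them. A reader who takes 80% as the power of the primary analysis is relying on an evaluable number that the plan has not shown it will reach.

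The sentence also misnames the hypothesis. A non-inferiority trial rejects inferiority; rejecting non-inferiority would be the opposite conclusion.

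**Working it through.** **Inputs.** From Sample size considerations: control rate 10%, remote rate 12%, margin 2% (taken as percentage points), power 80%, loss 10%, 1068 per arm, 2136 in total. Type I error is 2.5% there and under Data management and analysis; it is taken as one-sided, since the side is not stated. Equal allocation is assumed because the target is equal per arm. The multiplier is (1.96 + 0.8416)² = 7.849.

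**Reproducing 1068.** With a pooled rate of 11% and a distance of 4 points:
- n = 7.849 × 2 × 0.11 × 0.89 / 0.04² = 960.5, so 961
- 961 / 0.9 = 1067.8, so 1068

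With unpooled variance, 0.10 × 0.90 + 0.12 × 0.88 = 0.1956, the result is 960, and 960 / 0.9 gives 1067. So 1068 is the figure after inflation for loss. Had 1068 been the number analysed, enrolment would be 1068 / 0.9 = 1187 per arm, or 2374 in total, not 2136. Uninflated figures near 1068 need inputs that the protocol does not state: 1047 at 5% type I error and 90% power, or 1037 with equal 12% rates and a 4-point margin.

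**Power on the calculation's own terms.** Power = Φ(0.04 / SE − 1.96), with SE = √(0.09/n_control + 0.1056/n_remote). At 961 per arm, SE = 0.01427 and power is 80.1%. The extra exclusions below are assumed percentages of those enrolled, on top of the 10% loss; the protocol gives no rate.

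| Extra exclusion | n left in an affected arm | Power, remote arm only | Power, both arms |
|---|---|---|---|
| 0% | 961 | 80.1% | 80.1% |
| 5% | 908 | 78.8% | 77.8% |
| 10% | 854 | 77.5% | 75.3% |
| 20% | 748 | 74.2% | 69.6% |
| 30% | 641 | 70.1% | 62.9% |

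For comparison, 1068 analysed per arm with no exclusions would give 84.0% on the same terms.

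**Whether those terms hold.** The outcome is complications, so a higher rate is worse. The distance from the expected difference to the margin is 0.02 − (0.12 − 0.10) = 0. Power is then Φ(−1.96) = 2.5% at any n, with or without exclusions. The 4-point distance arises only if the expected 2-point excess is counted in favour of remote care. With equal true rates of 10%, SE = √(0.18/961) = 0.01369 and power = Φ(0.02/0.01369 − 1.96) = 31%.

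**The case against.** The strongest reply is that the size of the problem is not shown. No switching or exclusion rate appears anywhere, and 5% extra exclusion in the remote arm would cost little more than one point of power. That stands, and the table is a range of assumptions, not an estimate.

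Three stronger readings are tempting and are not supported:
- A reader might infer that everyone who changes visit mode is dropped. The 25% phone allowances contradict this for control and video participants.
- A reader might infer that the authors expect frequent switching. The Discussion only says that it might worsen the risk.
- A reader might assume equal exclusions in both arms. The one exclusion stated without tolerance, for face-to-face visits, applies to the remote arm, so the remote-only column deserves at least equal weight.

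It can also be said that some discontinuations may have been meant to fall within the 10%, and that the blinded review at 50% of recruitment can revise the assumptions. The article does not settle the first. On the second, the review is justified by scarce data on the primary endpoint; per-protocol evaluability is not named, and there is no stated assumption about it to revise.

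Finally, the enrolment target is clear from the 2136, so the word for 1068 changes no analysis by itself. That is fair; its effect is to overstate the evaluable number by about 107 per arm (1068 − 961).

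**Conclusion.** The point holds in limited form. The 1068 per arm is the enrolled number, with about 961 evaluable after 10% loss, and the null hypothesis is misnamed. The stated 80% has no stated allowance for exclusions from the primary set other than loss to follow-up. If 5% to 30% more were excluded, power on the plan's own working would be about 79% to 70% (remote arm only) or 78% to 63% (both arms), assuming a one-sided 2.5% level and an absolute margin.

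A reader might infer that 80% would be met if only the exclusions were provided for. It would not: the expected excess equals the margin, so the stated rates give 2.5% power whatever the allowance, and equal 10% rates give about 31% at 961 per arm. The allowance is the smaller problem, but it remains once the rates and margin are put right.

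**What to change.** 1. Reconcile the assumed event rates with the 2% margin. Until that is done, any restated power only repeats an unsound figure.
2. Then rewrite the paragraph with enrolled and evaluable numbers stated separately: 1068 and about 961 per arm if the present target stays.
3. Give power for the per-protocol set and for the intention-to-treat set over a range of exclusion rates, labelled as assumptions and shown by arm.
4. Say that the trial aims to reject inferiority.
5. Add the observed per-protocol evaluability rate to the assumptions examined at the blinded 50% review.

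The cost is rewording and a less favourable stated power. Restating needs no extra patients, but holding a chosen power might. On the present working, keeping 960 analysed with 10% extra exclusion in both arms would take 960 / 0.8 = 1200 enrolled per arm. That figure only illustrates scale, since it inherits the 4-point distance.
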